### Therapy

Three different cohorts will be treated in this study: healthy volunteers, patients with RRMS and ongoing IFN-β treatment and patients with RRMS starting on IFN-β treatment. Patients and healthy volunteers will receive three doses of 44 μg open-label Interferon-β-1a (Rebif®) within nine days as recommended in the standard treatment schedule. MS patients already on IFN-β treatment will only receive one dose of IFN-β while included in this study. Dose modification or adjustments for either group are not intended by the trial protocol. After the study is finished MS patients will be treated at the discretion of the responsible physician.

At or before the screening visit, each patient has to provide written informed consent to the study. The screening consists of reviewing inclusion and exclusion criteria, demographic variables, medical history, concomitant medication, physical and neurological examination and vital signs, electrocardiogram (ECG) and laboratory tests are obtained by a study nurse and the treating physician. MRI, EDSS scoring and psychometric tests are performed. Laboratory tests include complete blood count, serum chemistry, coagulation, drug screening, pregnancy test and urine analysis.

At baseline visit vital signs and ECG as well as the occurrence of adverse events and changes of the concomitant medication are documented. Screening and baseline visit are performed within 14 days. Then IFN-β-1a treatment is started and blood for the analysis of cytokine serum levels, miRNA- and mRNA-expression as well as experimental immune evaluation is collected at five different times within 24 h. Thereupon, the study is finished for MS patients that have been already on IFN-β treatment. Healthy volunteers as well as MS patients that have been started on IFN-β will continue with study visits at days 3, 5 and 8 with documentation of adverse events and concomitant medication and collection of further blood samples for analysis of immune activation. At day nine healthy volunteers as well as MS patients will have the final visit with the same assessments as described for the screening and baseline visit, including magnetic resonance imaging (MRI) assessment. Additional, blood for analysis of immune activation is collected.

### Magnetic resonance imaging

To characterize neurobiological correlates of the action of IFN-β, changes in base perfusion levels, in limbic reactivity to emotionally laden stimuli, in the neural response to potential rewards, and their association with psychometric parameters will be assessed in healthy volunteers through noninvasive neuroimaging techniques. All MRI scans are performed according to a standardized MRI protocol and will be assessed centrally. MRI scans of the brain will be performed only in the healthy volunteers at the screening and at the final visit. Functional neuroimaging of limbic reactivity will be performed to analyze both emotional reactivity and the capacity of participants to down-regulate it.

### Statistical analysis

The **sample size** is set on 20 healthy volunteers and 20 patients with established IFN-β treatment and 10 MS patients naïve to IFN-β treatment. Since this is a study to gain information about the distribution of the expression values in these patients, this sample size is not based on statistical considerations.

**Primary target variables** of the study is the estimation of changes in serum level of type I IFN and type I IFN-dependent proteins (e.g. CXCL10) as well as of changes in mRNA expression of type I IFN-dependent genes (e.g. CXCL10, MxA and RIG-I) after a dose of IFN-β treatment in healthy volunteers and in patients with RRMS. For this purpose, the median of the levels will be calculated separately for the two study groups. 95 % confidence intervals for the medians will be calculated using bootstrap. As additional descriptive parameters mean, standard deviation, minimum, maximum and the quartiles of the distribution will be calculated for each group and variable. A comparison of the expression levels between patients and controls will be performed with a two-sided Mann–Whitney-Wilcoxon test. These tests are regarded as descriptive analysis, their result are reported as p-values.

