## Methods/Design

ResI is a single center, prospective, open label, non-randomized phase I clinical trial. Three different cohorts (healthy volunteers, patients with RRMS and ongoing IFN-β treatment and patients with RRMS starting on IFN-β treatment) will receive three applications of standard IFN-β therapy for nine days. As a comparison between pre- and post-treatment is performed, no placebo group is planned. The study will be conducted according to the principles of the german medicinal products act, ICH-GCP, and the Declaration of Helsinki on the phase I unit of the Institute of Clinical Chemistry and Clinical Pharmacology and in the Department of Neurology, both University Hospital Bonn. The local ethics committee and the German competent authorities (Federal Institute for Drugs and Medical Devices) already approved this study. The Clinical Study Core Unit will perform the clinical procedures, monitoring, safety management, data management, and data analysis of the study. The Institute of Clinical Chemistry and Clinical Pharmcology, that includes the central laboratory of the University Hospital Bonn will perform the routine as well as experimental laboratory analysis.

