### Secondary objectives

Secondary objectives of this trial are the analysis of the miRNA- and gene-expression pattern in response to recombinant IFN-β in peripheral blood mononuclear cells and serum of healthy volunteers as well as RRMS patients, the comparison of the response to IFN-β between healthy volunteers, patients with RRMS naïve to IFN-β treatment and RRMS-patients with established IFN-β treatment, correlation of side effects of IFN-β treatment with immune- or miRNA-response to IFN-β. Potential central nervous adverse drug effects such as emotional changes associated with IFN-β treatment (depression, anxiety, impulsivity) will be assessed by psychometric testings and noninvasive neuroimaging techniques.

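### The statistical section analyses two groups although three cohorts are enrolled; read naturally, it merges IFN-β-naïve and established RRMS patients in the primary medians and in the only between-group test described

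*Protocol article*

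**What the plan says.** The Methods/Design section of the protocol article defines the population as "Three different cohorts (healthy volunteers, patients with RRMS and ongoing IFN-β treatment and patients with RRMS starting on IFN-β treatment". The Abstract, Inclusion criteria and Therapy sections name the same three cohorts. The Primary objective covers RRMS patients both continuing and starting treatment. The Secondary objectives include "the comparison of the response to IFN-β between healthy volunteers, patients with RRMS", with the RRMS patients split there into naïve and established.

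The Statistical analysis section begins with all three cohorts: "20 healthy volunteers and 20 patients with established IFN-β treatment and 10 MS patients naïve to IFN-β treatment". It adds that "this sample size is not based on statistical considerations". It then defines the primary target variables as changes "after a dose of IFN-β treatment in healthy volunteers and in patients with RRMS", without splitting the patients. Next come the estimation rule, "the median of the levels will be calculated separately for the two study groups", with 95% bootstrap intervals for those medians, and the test: "A comparison of the expression levels between patients and controls will be performed with a two-sided Mann–Whitney-Wilcoxon test". The tests are called descriptive and are reported as p-values. The section gives no significance level.

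**The concern.** The number of analysis groups does not match the number of cohorts, and the mismatch sits in the primary estimation. If the sentence is followed as it reads, patients receiving their first IFN-β dose and patients on ongoing treatment share one median, one interval and one side of the rank test.

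Two things are at stake. First, the article's stated use of these results is to judge whether type I IFN induced by the RIG-I ligand lies below or above that of standard IFN-β treatment, and so to guide dose steps. A median over two exposure states is a poor reference for either. Second, the article includes both volunteers and patients because they may respond differently. A patient-versus-control difference could then come from earlier treatment and not from disease. A real difference could also be diluted if the two patient cohorts differ.

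**Working it through.** There is no sample-size calculation to reproduce, because the article says that none was made. The cohort sizes agree between the Abstract and the Statistical analysis section: 20 + 20 + 10 = 50.

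**Step 1: which two groups?** The sentence before the estimation rule names healthy volunteers and RRMS patients, and the test names patients and controls. Both point to 20 healthy volunteers against 20 + 10 = 30 RRMS patients.

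**Step 2: imbalance in prior exposure.** Under Inclusion criteria, all healthy volunteers are naïve to IFN-β.
- Patients already on IFN-β: 20/30 = 67%.
- Controls already on IFN-β: 0/20 = 0%.
- Naïve to established within the patient group: 10:20 = 1:2.

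**Step 3: illustration of what merging could do.** The article gives no SDs, effect sizes or significance level, so everything in this step is assumed: normal data, SD 1 in each cohort, no disease effect, prior exposure shifting the level by d SD, a nominal two-sided 0.05, and 4,000 simulated trials per row. The pooled median m solves (2/3)·Φ(m − d) + (1/3)·Φ(m) = 0.5.

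| d (SD) | Pooled RRMS median (SD) | Pooled 30 vs healthy 20, p<0.05 | Naïve 10 vs healthy 20, p<0.05 | Naïve 10 vs established 20, p<0.05 |
|---|---|---|---|---|
| 0 | 0.00 | 4.6% | 3.9% | 4.3% |
| 0.5 | 0.33 | 19.2% | 4.0% | 21.3% |
| 1.0 | 0.68 | 55.4% | 4.7% | 66.8% |
| 1.5 | 1.04 | 86.2% | 4.8% | 94.3% |
| 2.0 | 1.44 | 98.0% | 4.3% | 99.8% |

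With no disease effect, the pooled comparison responds to exposure alone. The naïve-versus-healthy comparison stays near the nominal level.

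Dilution is also possible. If naïve patients are shifted by +1 SD and established patients by 0, the pooled test gives p<0.05 in about 16% of trials, against about 65% for naïve versus healthy.

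**Step 4: cost of splitting.** The difference detectable with 80% power at two-sided 0.05 (normal approximation) is (1.96 + 0.84)·√(1/n₁ + 1/n₂):
- 20 vs 30: 0.81 SD
- 20 vs 20: 0.89 SD
- 20 vs 10: 1.09 SD

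An order-statistic interval for a median with at least 95% coverage runs from the 2nd to the 9th of 10 values (97.9%), from the 6th to the 15th of 20 (95.9%), and from the 10th to the 21st of 30 (95.7%). With 10 patients it spans nearly the whole sample.

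**The case against.** **Pooling is inferred.** The article never says that the RRMS cohorts are combined. The section lists them separately a few lines earlier and promises descriptive statistics for each group. The word two may be a drafting slip. This stands as a limit on the claim, but not as a reason to leave the text: if it is followed, it merges two cohorts, and if it is a slip, the primary estimation is misstated.

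**An article condenses.** It may leave secondary analyses to a fuller document. That is accepted, and the absence of a secondary analysis is not raised here. The grouping for the primary analysis, however, is stated, and it conflicts with the article's own design.

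**The three-way question.** A reader might infer that this comparison has become impossible. The documents do not support that. Cohorts are enrolled and identified separately, and all give the five blood samples within the first 24 hours after a dose.

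**The simulated rates.** A reader might take them as the trial's error rates. They are not. The shifts and the 0.05 threshold are assumptions, and the tests are descriptive. If change from baseline is analysed, a stable offset from earlier treatment cancels and only a different response to the dose remains. The section speaks both of changes and of levels, so the size of the bias cannot be fixed.

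**Clean effects.** A reader might treat naïve versus healthy as a pure disease effect, or established versus naïve as a pure exposure effect. The trial is non-randomised and patients start treatment on routine clinical grounds, so neither holds.

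**Conclusion.** The primary analysis as worded does not fit the design and should be corrected. That two analysis groups are set against three cohorts is certain from the text. That the 30 RRMS patients are merged is the natural reading, but it is not explicit. On that reading, the patient median and its interval describe a 1:2 mixture, and the only between-group test described carries an exposure imbalance of 67% against 0%. The confounding is partial, because 10 of the 30 patients are naïve, and its size is unknown. The simulated figures show only that it could matter under moderate assumed shifts.

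Because the primary aim is to determine levels, the question of which group each median and interval describes matters more than any p-value. Enrolment, sampling and data collection are unaffected, so this is a point that should be fixed and not one that endangers the trial.

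**What to change.** In the Statistical analysis section:

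1. Replace the two study groups by the three cohorts, and report the median, bootstrap interval and other descriptive statistics for each.
2. Replace the single patients-versus-controls comparison by named, descriptive Mann–Whitney contrasts: naïve RRMS versus healthy volunteers, both at first dose; established versus naïve RRMS; and established RRMS versus healthy volunteers as supportive.
3. State that these contrasts are non-randomised and do not isolate disease or prior exposure.
4. Label any summary over all RRMS patients as supplementary.

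The change is to analysis wording only and needs no new data. The cost is precision: wide intervals for the cohort of 10, and a detectable difference of about 1.09 SD for 20 vs 10 instead of about 0.81 SD for 20 vs 30, under the assumptions in the working.

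### The primary variable is the change after dosing, but the statistics stated for it are medians and between-group tests of levels; no stated analysis estimates the within-subject change

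*Protocol article*

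**What the plan says.** Under Statistical analysis, the protocol article gives the primary target as "the estimation of changes in serum level of type I IFN and type I IFN-dependent proteins", together with "changes in mRNA expression of type I IFN-dependent genes", after a dose of interferon-beta. The next sentence names the statistic meant to serve that aim: "the median of the levels will be calculated", one for each of two groups. The article adds that 95% "confidence intervals for the medians will be calculated using bootstrap". The only test named is a two-sided Mann-Whitney-Wilcoxon comparison of expression levels between patients and controls. It is labelled descriptive, and no significance level is set.

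Methods/Design explains why there is no control arm: "As a comparison between pre- and post-treatment is performed, no placebo group is planned".

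Under Inclusion criteria, one of the three cohorts consists of patients already on interferon-beta. On sampling, Therapy says "Then IFN-β-1a treatment is started and blood for the analysis of cytokine serum levels" and other markers is collected at five times within 24 hours. Only the healthy and newly starting cohorts are sampled after that.

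**The concern.** The variable and its statistic do not match. A median of levels does not estimate a change, and a rank test of levels between groups does not compare changes. Each cohort is an uncontrolled group, so the comparison of a subject with himself or herself before dosing is the study's only control, and the article attaches no statistic to it.

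The mismatch matters most for the cohort comparison. Secondary objectives asks how the response differs between healthy volunteers, untreated patients and established patients. The established patients may start from a different level because of earlier injections. The article describes no washout, so this is plausible, but it is an inference and not a documented fact. A contrast of post-dose levels would then mix the response to the study dose with what was there beforehand. The Discussion intends to use these results to judge whether type I interferon induced by the RIG-I ligand lies below or above that of standard treatment. An induced amount is a quantity relative to pre-dose.

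**Working it through.** **Text side by side**

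| Element | What the article states |
|---|---|
| Primary variable | change after a dose |
| Estimate for it | median of levels, per group |
| Interval | 95% bootstrap, for those medians |
| Test | Mann-Whitney-Wilcoxon on levels, patients v controls |
| Control for the missing placebo | pre/post comparison |
| Statistic for pre/post | none stated |

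Medians listed at each sampling time would not close the gap. A difference of two medians is not in general the median of the within-subject differences, and separate intervals ignore the pairing.

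**Inputs.** The article gives group sizes (20 healthy, 20 established, 10 newly starting) and no SD, correlation, effect size or baseline difference. It says the sample size has no statistical basis, so there is no figure to reproduce. Everything below except the group sizes is assumed: log-scale normal values, SD 1 before and after dosing, pre/post correlation ρ = 0.6, and 3,000 simulated trials per scenario. The count is two-sided p<0.05. Patients are pooled to 30 because the article speaks of two study groups.

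**Scenario A: equal induction in everyone; the 20 established patients start b SD higher and keep that excess after dosing.**

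| b | Levels test, p<0.05 | Changes test, p<0.05 |
|---|---|---|
| 0 | 5% | 5% |
| 0.5 | 18–19% | 4–5% |
| 1 | about 55% | 4–5% |
| 2 | 98% | 4–5% |

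At b = 1 the average shift over the pooled patients is 20 × 1 / 30 = 0.67 SD. The simulated median difference in levels is also about 0.67 SD, although no true difference in response exists. With only the 20 established patients against the 20 healthy volunteers, the levels test gives 31% at b = 0.5 and 84% at b = 1.

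**Scenario B: a ceiling. Established patients start 1 SD higher but reach the same post-dose level.** The levels test gives about 5%. The changes test gives about 65% (64% and 66% in two runs). The smaller change is real here, but it reflects prior treatment.

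**Precision.** With SD 1:
- Variance of a level: 1.
- Variance of the raw change: 2(1 − ρ). This is 1.4 at ρ = 0.3, 1.0 at 0.5 and 0.8 at 0.6.
- Residual variance of the post-dose value adjusted for pre-dose: 1 − ρ². This is 0.75, 0.64 and 0.36 at ρ = 0.5, 0.6 and 0.8.

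The raw change is therefore noisier than the level when ρ is below 0.5. Adjustment is never noisier.

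**What adjustment does in these cohorts.** The expected adjusted contrast is the post-dose difference minus ρ times the pre-dose difference. For established patients v healthy volunteers at b = 1, it is 1 − 0.6 = 0.4 SD in scenario A and 0 − 0.6 = −0.6 SD in scenario B. Adjustment and raw change thus answer different questions when cohorts are not randomized.

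**The case against.** The strongest reply has four parts.

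- **A condensed article.** The full protocol and SAP are not shown, and Methods/Design says the pre/post comparison is performed. A reader might infer that it will never be analysed; the document does not support that. What stands is narrower: the article does state a statistic for the primary variable, and that statistic does not estimate it. That is more than detail left for later.
- **The pre-dose sample.** A reader might infer from Therapy that no pre-dose biomarker sample is taken, since the draws are mentioned after the start of treatment and the baseline visit lists none. The text does not say that all five draws are post-dose, and speaking of changes presupposes one that is not. This is a point to confirm, not a defect.
- **Levels have a use.** The Background treats the level reached under standard treatment as the yardstick for the ligand, and the Primary objective includes the interferon-beta protein level. This stands in full: change should be added to levels and should not replace them.
- **The simulation follows from its assumptions.** This also stands. Scenario A favours the change by construction, and scenario B reverses the pattern. With descriptive tests and no significance level, 55% is not a false-positive rate of this trial.

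Reading levels loosely as levels of the change would remove the mismatch, but the word is used of the measurements themselves, and the test is described as one of expression levels.

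**Conclusion.** The point holds in this form: followed as written, the stated analysis does not estimate the stated primary variable, and the comparison offered in place of a placebo group has no stated statistic. The mismatch rests on the text alone.

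Its numerical effect depends on assumptions. If the established cohort starts no higher, the levels test shows no distortion. If it starts 0.5 to 2 SD higher and carries this through, the pooled levels test gives p<0.05 in roughly 18% to 98% of trials with no true difference in response. Under a ceiling the change is the scale that differs. A reader might conclude that analysing changes would by itself isolate the response in treated patients; it would not. Neither scale alone separates response from carry-over, which is why both must be shown.

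**What to change.** 1. Define the primary quantity for each marker as the within-subject change (difference or log ratio) from a named pre-dose sample to a named post-dose time. For contrasts involving the established cohort, that time must fall within the first 24 hours, since this cohort is not sampled later.
2. Report its median with a 95% bootstrap interval, resampling subjects, for each of the three cohorts and not for two groups.
3. Make cohort contrasts on the change, or on the post-dose value adjusted for pre-dose. State in advance which one leads, since the two can differ in these non-randomized cohorts.
4. Keep pre-dose and post-dose levels in the same table, noting that the established cohort's pre-dose value is not an untreated baseline.
5. Confirm that one of the five draws in Therapy is taken before the study dose.

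The cost is mostly wording and a little more analysis. The raw change is noisier than the level if the pre/post correlation is below 0.5. If all five draws were meant to be post-dose, one post-dose time point is lost.

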### Inclusion criteria

Three different cohorts will be studied: 1.) Healthy volunteers naïve for IFN-β treatment. 2.) patients with relapsing-remitting MS (RRMS) according to McDonald's criteria and baseline expanded disability status scale (EDSS) score from 0 to 6.0 starting on IFN-β treatment according to routine clinical criteria. 3.) Patients as described above but already on IFN-β treatment. Additional inclusion criteria applicable for all individuals in this study: age between 18 and 65 years, adequate bone marrow-, renal-, hepatic- and clotting-function. Male and female patients with reproductive potential have to use an approved contraceptive method and a negative serum pregnancy test must be obtained prior to treatment start in female patients with childbearing potential. All individuals need to have signed the informed consent form.

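### The volunteer-versus-RRMS comparison is an unadjusted rank test between non-randomised cohorts not described as matched, so age or sex imbalance may create or mask a difference in IFN-β response

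*Protocol article*

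**What the plan says.** The protocol article (Methods/Design) calls the study a "single center, prospective, open label, non-randomized phase I clinical trial". Cohort membership follows from diagnosis and IFN-β history: "20 healthy volunteers and 20 patients with established IFN-β treatment and 10 MS patients naïve to IFN-β treatment" (Statistical analysis).

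The Inclusion criteria apply one range to everyone, "age between 18 and 65 years", and admit both sexes. Matching of volunteers to patients is not described. Screening records "demographic variables, medical history, concomitant medication, physical and neurological examination" among other items (Therapy).

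The one between-group method named is this: "A comparison of the expression levels between patients and controls will be performed with a two-sided" Mann–Whitney–Wilcoxon test (Statistical analysis). No covariate or stratification goes with it. Its status is limited at once: "These tests are regarded as descriptive analysis, their result are reported as p-values". Of the cohort sizes the same section says that "this sample size is not based on statistical considerations".

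The comparison nevertheless has a purpose. Secondary objectives lists comparing the IFN-β response across the three cohorts. Background says both populations are studied because their responses might differ. The Discussion gives excluding such a difference as a reason for including both.

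**The concern.** A two-sample rank test compares the cohorts as they happen to be composed. Volunteers and RRMS patients are recruited by different routes, and nothing described in the article makes their age or sex distributions alike. If such a characteristic differs between the cohorts and also influences CXCL10, MxA, RIG-I or another marker, its effect is mixed into the contrast.

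The error can go either way. A spurious difference could suggest that the volunteer benchmark does not carry over to patients. A masked difference would matter more for the stated wish to exclude one, because the absence of a visible gap would be taken as reassurance. The Discussion itself faults earlier work for confounding factors such as concomitant medication, yet the test named here takes no confounder into account.

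**Working it through.** **No planned figure to reproduce.** The sample size is stated to have no statistical basis, and no effect size, SD, alpha or power is given. The check therefore asks how far a demographic imbalance would pass into the named test.

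**Inputs from the document.** 20 volunteers, 20 patients on IFN-β and 10 starting it; hence 20 v 20, 20 v 10, or 20 v 30 if patients are pooled (20 + 10 = 30). The test is a two-sided Mann–Whitney–Wilcoxon test without covariates.

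**Assumed inputs (not in the document).** The degree of imbalance, the covariate's effect on the marker, and a 5% threshold used only as a yardstick.

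**Step 1: size of the bias, binary covariate.** Bias = covariate effect × difference in prevalence. With assumed prevalences of 40% and 75%, the difference is 0.75 − 0.40 = 0.35.

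| Covariate effect (SD) | Bias in the contrast (SD) |
|---|---|
| 0 | 0 |
| 0.5 | 0.5 × 0.35 = 0.175 |
| 0.8 | 0.8 × 0.35 = 0.28 |
| 1.0 | 1.0 × 0.35 = 0.35 |

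If the prevalences are equal, the bias is zero whatever the effect.

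**Step 2: what the unadjusted test does with it.** Simulation with no true cohort effect, 4,000 trials per setting, 20 v 30: p falls below 0.05 in about 8%, 14% and 18% of trials at effects of 0.5, 0.8 and 1.0 SD. A linear model containing the covariate stays at about 5%.

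**Step 3: the same check with a continuous covariate.** The imbalance is in SD of the covariate, and rho is its assumed correlation with the marker. Share of trials with p < 0.05, no true cohort effect:

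| Cohorts | Imbalance | rho 0 | rho 0.2 | rho 0.4 | rho 0.6 |
|---|---|---|---|---|---|
| 20 v 20 | 0.5 SD | 5.6% | 6.0% | 9.4% | 14.5% |
| 20 v 20 | 1.0 SD | 5.1% | 9.6% | 21.5% | 44.1% |
| 20 v 10 | 1.0 SD | 4.1% | 6.6% | 13.9% | 29.0% |
| 20 v 30 | 1.0 SD | 5.1% | 9.2% | 23.7% | 50.9% |

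With no imbalance and rho 0 the test rejects in 4.5% to 4.7% of trials. The covariate-adjusted model stays between 4.2% and 5.5% in every setting. Both ingredients are needed: without an imbalance, or without a relation to the marker, the rank test behaves as it should.

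**Step 4: scale.** The difference detectable with 80% power at an assumed two-sided 5% is (1.96 + 0.84) × √(1/n₁ + 1/n₂). This gives about 0.89 SD for 20 v 20, 1.09 SD for 20 v 10 and 0.81 SD for 20 v 30. A bias of 0.35 SD is 0.35/0.81 ≈ 43% of the last figure. That is not negligible when a small observed gap is taken as reassurance.

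**The case against.** The strongest reply has four parts.

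- **The full protocol or SAP may adjust.** This is a condensed article, and covariate models are often left to those documents. A reader might infer that no adjusted analysis is planned; the article does not support that. What stands is that the one between-group method it does name is unadjusted.
- **The tests are labelled descriptive.** The article sets no alpha, so the rejection rates above are measured against a threshold that the plan does not use. That is correct, and those rates are only a yardstick. The label removes the confirmatory claim, but a descriptive difference is confounded in the same way.
- **No causal claim is made.** The article does not say that a difference will be attributed to RRMS, and the response in each population as enrolled is a legitimate benchmark for later dosing. This protects the within-cohort medians and their bootstrap intervals. It does not protect the cohort contrast when that contrast is used to exclude a difference in response.
- **Adjustment has limits.** Adjusting for the pre-dose level is contestable: in patients on ongoing IFN-β that level may already reflect treatment, which is what defines their cohort. This stands and shapes the fix.

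A reader might also infer that demographic differences will appear as differences in response. The article supports only that they may, since it gives neither an imbalance nor a covariate effect. Nor does it list age and sex as collected items: it says demographic variables, and the age limits and the pregnancy-test rule imply that both are known. Body weight is not mentioned.

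**Conclusion.** The point holds as a limit on the between-cohort comparison. The cohorts are non-randomised and not described as matched, the named test is unadjusted, and the comparison serves a secondary objective and a stated reason for the design. An age or sex imbalance related to the markers may therefore create or mask a difference.

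How large the bias would be cannot be determined from the document. The range of 0.175 to 0.35 SD rests on an assumed 40% v 75% split and assumed effects of 0.5 to 1.0 SD, and it is zero if either ingredient is absent. The primary within-cohort estimates are unaffected. This is an inexpensive improvement to a descriptive comparison and not an error that invalidates the study.

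**What to change.** Keep the Mann–Whitney–Wilcoxon test as the unadjusted descriptive comparison. Beside it, pre-specify a linear model on the log2 change from pre-dose, with cohort at three levels, age and sex, and report adjusted fold ratios between cohorts with 95% CI. Tabulate baseline characteristics by cohort, and state that unadjusted differences will not be attributed to RRMS. If the full protocol or SAP already contains such a model, a sentence saying so is enough.

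Leave the pre-dose level out of the main model as a covariate, for the reason given above; show it at most as a sensitivity analysis.

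The cost is analysis wording; no extra subjects, visits or samples are needed. The model uses two cohort contrasts, age and sex, so four parameters beyond the intercept with 50 subjects, and it assumes a log scale. With one cohort of only 10, no further covariates should be added. Adjustment for age and sex cannot separate disease from prior IFN-β exposure in the ongoing-treatment cohort, and the report should say so.
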